### Participants

Sixty-two participants with a recent isolated medial APM will be recruited from metropolitan Melbourne, Australia. The primary recruitment strategy will be via screening of surgical records of several Melbourne-based orthopaedic surgeons. Additionally, we will recruit individuals by advertising through University staff newsletters and Facebook. To be eligible, participants must be aged between 30–50 years and have undergone an isolated medial APM in the past 3–12 months.

The exclusion criteria are:

i) an average overall pain severity ≥3 out of 10 on an 11 point numerical rating scale in the past week

ii) signs of moderate to severe radiographic knee OA (Kellgren-Lawrence grade >2) [47]

iii) full tears of the anterior or posterior cruciate knee ligaments

iv) anterior or posterior ligament reconstructions

v) spinal or lower extremity pain (other than the affected knee) that limits everyday activities or required treatment in the past month

vi) high levels of physical activity defined as participation in an organised team or individual sport that requires regular competition and requires some form of systematic training [48]

vii) history of lower limb surgery (other than knee arthroscopy)

viii) other form of arthritis, diabetes, cardiac circulatory conditions that limit everyday activities (as determined by the Self-administered Co-morbidity Questionnaire)[49]

ix) neurological condition such as Parkinson’s disease, multiple sclerosis or stroke

x) any condition precluding safe participation in exercise

(xi) unable to complete the study protocol

(xii) inadequate written or spoken English

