### Sample size

A sample size of 62 participants ensures adequate power to detect significant changes in the external peak KAM and KAM impulse after the 12-week study period. As previously mentioned, a 14% reduction in peak KAM has been reported during one-leg rise in an uncontrolled study of people with knee OA following a neuromuscular exercise program [36]. Importantly, this reduction in peak KAM may be clinically relevant as it potentially corresponds to an approximate 2-fold reduction in risk of OA disease progression [25]. Therefore, we anticipate that a minimum 10% reduction in the peak KAM may be feasible with our neuromuscular program and that such a change may be potentially clinically meaningful. We anticipate that the peak KAM will remain unchanged in our control group participants. Based on our previous peak KAM data from APM participants [65], a 10% reduction equates to an absolute change of approximately 0.2 Nm/(BWxHT)%. Cautious estimates of the standard deviation of change scores are 0.3 Nm/(BWxHT)%, based on knee OA data from our laboratory investigating conservative treatments for knee OA [33]. Despite little being known about the clinically meaningful difference for KAM impulse or the response to interventions, we speculate a 10% change in KAM impulse is also feasible and potentially clinically meaningful following a neuromuscular intervention. We also anticipate that the KAM impulse will remain unchanged in our control group participants. Based on our previous KAM impulse data from APM participants [65], a 10% reduction equates to an absolute change of approximately 0.09 Nm.s/(BWxHT)%. Estimates of the standard deviation of change scores are 0.10 Nm.s/(BWxHT)% based on APM data from our laboratory where KAM impulse did not change over 2 years [65]. Therefore, a total of 27 participants per group is required to detect our anticipated changes in peak KAM and KAM impulse (assuming standard deviations as stated above) between the groups with 80% power (2 sided test, alpha=0.05). To account for 15% attrition, we will recruit 31 participants per group.

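### Recruiting 31 per group falls just short of covering 15% attrition from a requirement of 27 (26.35 would remain); a minor arithmetic correction

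*Protocol article*

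**What the plan says.** The Sample size section of the protocol article states that "a total of 27 participants per group is required to detect our anticipated changes in peak KAM and KAM impulse", with 80% power at a two-sided alpha of 0.05. The next sentence makes the allowance for loss to follow-up: "To account for 15% attrition, we will recruit 31 participants per group". Two groups of 31 give the 62 on which the section opens: "A sample size of 62 participants ensures adequate power to detect significant changes in the external peak KAM and KAM impulse".

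The Data and statistical analysis section plans an intention-to-treat comparison of everyone randomised, with multiple imputation of missing follow-up data and regression adjusted for the baseline value and sex.

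**The concern.** An attrition allowance is meant to leave the required number with outcome data after the stated loss. Here the requirement is a whole number (27) and the loss a stated percentage (15%), so the step can be checked exactly, and 31 does not quite pass. At stake is the accuracy of one sentence: how much loss the design absorbs before it drops below its own requirement. The same total is carried into the abstract and the Participants section as the recruitment target.

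**Working it through.** **Inputs, all from the Sample size section.** Required n = 27 per group; attrition 15%; recruited n = 31 per group (62 in total); two-sided alpha 0.05. Peak KAM: difference 0.2, SD of change 0.3, so d = 0.2 / 0.3 = 0.667. KAM impulse: difference 0.09, SD of change 0.10, so d = 0.9. No change is assumed in the control group.

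**1. Reproducing the stated figure.** 27 × (1 + 0.15) = 31.05, which rounds to 31. This matches, but the article gives no formula, so the route is an inference.

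**2. The inflation that covers the loss.** n / (1 − attrition) = 27 / 0.85 = 31.76, so 32 per group (64 in total). Check: 32 × 0.85 = 27.2, which is at least 27.

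**3. What 31 leaves.** 31 × 0.85 = 26.35 per group, a gap of 27 − 26.35 = 0.65. Over both groups, 62 × 0.85 = 52.7 against 2 × 27 = 54.

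**4. The loss that 31 absorbs.** 1 − 27/31 = 4/31 = 12.9%. In whole people, losing 4 leaves 27 and losing 5 (5/31 = 16.1%) leaves 26.

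**5. Effect on power.** Two-sided, two-sample t-test with n per group, noncentrality d × √(n/2) and 2n − 2 degrees of freedom:

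| n per group | Peak KAM, d = 0.667 | KAM impulse, d = 0.9 |
|---|---|---|
| 27 | 67.2% | 90.1% |
| 26.35 | 66.1% | 89.3% |
| 26 | 65.4% | 88.9% |

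Going from 27 to 26.35 costs about 1 point in either column.

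**6. The same step, taking the claimed 80% at 27 at face value.** Under the normal approximation the noncentrality is 1.960 + 0.842 = 2.802. Scaling by √(26.35/27) = 0.988 gives 2.768. Power is then Φ(2.768 − 1.960) = Φ(0.808), about 79%, again a loss of about 1 point.

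**The case against.** The strongest case on the other side is that this is a rounding matter. The gap is 0.65 of a person, no whole-number loss from 31 equals 15%, and a loss of 4 leaves exactly 27. That stands as a judgement of size. It does not make the sentence correct, because the inputs are exact and even ordinary rounding of 31.76 gives 32.

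A second argument is that the regression adjusts for baseline, which the sample size calculation does not use. To offset the gap, adjustment would have to remove 1 − 26.35/27 = 2.4% of the variance, that is, a baseline–change correlation of about √0.024 = 0.16. This is plausible, but the article gives no such correlation, so it remains an assumption.

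Third, division would also give 31 if the unrounded requirement had been 26.35 or less and was then reported as 27. The article cannot settle this, so multiplication should not be stated as fact. On the figures as printed, the mismatch remains either way.

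A reader might go further and infer that the trial will miss its own planned analysis number. The article does not support that. The 27 is the number required for power, not a planned count of analysed participants, and the analysis section includes everyone randomised, with missing follow-up imputed. Imputation does not in general restore the lost outcome information, so the attrition allowance still matters, but no stated analysis number is missed. Nor is there an error in the Participants section, where "Sixty-two participants with a recent isolated medial APM will be recruited from metropolitan Melbourne, Australia" makes no claim about attrition.

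**Conclusion.** The point holds as a minor correction. On the article's own figures, 31 per group covers about 12.9% attrition and not 15%; covering 15% from 27 needs 32. The shortfall is under one participant per group and about one percentage point of power, whether one uses the stated inputs or the claimed 80%. It would not alter the trial's conclusions. This rests on reading 27 as the number who should still provide follow-up data after losses, which is the only reading under which an attrition allowance has a purpose.

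The low peak KAM power in the table should not be attributed to the attrition step. It is already 67.2% at 27, because 27 does not follow from the stated peak KAM inputs: 2 × (0.3 × 2.802 / 0.2)² = 35.3, so 36 per group. That is a separate and much larger matter.

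**What to change.** Keep 62 and change one statement in the Sample size section, in either of two ways:

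- restate the allowance as up to about 13% attrition (4 of 31 lost, 27 retained in each group); or
- keep 15%, say that about 26 per group are then expected to give follow-up data, and report the power at 26 on the stated inputs: about 65% for peak KAM and about 89% for KAM impulse (two-sided t-test).

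The second is more informative, because the first carries the 27 forward unexamined. If the 27 is itself recalculated, redo the allowance by division. With 36 per group, for example, 36 / 0.85 = 42.4, so 43, whereas 36 × 1.15 = 41.4 would give 42 after rounding up.

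The cost is one edited sentence. Neither wording needs extra recruitment, which matters because the Timeline section reports that recruitment has already begun.

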### Data and statistical analysis

Data analysis will be performed in a blinded manner and main comparative analyses between the two groups will be performed using an intention-to-treat analysis using all randomised participants. Multiple imputation methods will be used to address missing follow-up data. Participant characteristics and baseline data will be summarised by descriptive statistics. T-tests or non-parametric tests, as appropriate will be used to determine baseline comparability between the two groups. One-way ANOVA will be used to determine baseline comparability between the two groups. A non-parametric test will be used to determine baseline comparability for categorical data. For each dependent variable, change scores for each participant will be calculated by subtracting the follow-up score from the baseline score. Regression analyses adjusted for baseline values of the dependent variable and sex (the stratification variable) will be used to compare changes between baseline and follow-up for each independent variable. Standard diagnostic plots will check model assumptions. All tests will be two-tailed and performed at the 5% significance level.

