**Methods/design:**

62 people aged 30–50 years who have undergone an arthroscopic partial medial meniscectomy within the previous 3 to 12 months will be recruited and randomly assigned to a neuromuscular exercise or control group using concealed allocation. The neuromuscular exercise group will attend 8 supervised exercise sessions with a physiotherapist and will perform 6 exercises at home, at least 3 times per week for 12 weeks. The control group will not receive the neuromuscular training program. Blinded assessment will be performed at baseline and immediately following the 12-week intervention. The primary outcomes are change in the peak external knee adduction moment measured by 3-dimensional analysis during normal paced walking and one-leg rise. Secondary outcomes include the change in peak external knee adduction moment during fast pace walking and one-leg hop and change in the knee adduction moment impulse during walking, one-leg rise and one-leg hop, knee and hip muscle strength, electromyographic muscle activation patterns, objective measures of physical function, as well as self-reported measures of physical function and symptoms and additional biomechanical parameters.

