### Primary hypothesis

The 12-week neuromuscular exercise program will reduce medial knee joint loading, as characterised by the peak external KAM during normal pace walking and one-leg rise, when compared to a control group not receiving the neuromuscular exercise program.

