For the one-leg rise task, participants will be seated in a standardised position with a chair height of 48cm, seat depth of 75% thigh length and 100° knee flexion. Participants will be instructed to flex the non-test knee holding the leg off the ground throughout the task, and rise from the seat using the test leg (leg being assessed) until standing upright, and then return to the seated position. If participants cannot rise from the seat, the chair height will be increased in increments of 2.5cm until the task can be achieved. Following two practice trials, three trials will be recorded and averaged for each leg. For the one-leg hop for distance task, participants will be instructed to stand on one foot with their arms across their chest and instructed to jump as far forward as possible and land steadily, without over-balancing on the same foot. Following, two practice trials at submaximal effort, three maximum trials where a complete foot lands on a single force plate will be averaged and collected for each leg. In an effort to minimise fatigue, three trials are considered adequate to assess the more demanding tasks (one-leg rise and one-leg hop). Reflective markers will be placed on the participant according to the University of Western Australia (UWA) marker set [54]. Data from the reflective markers (sample rate 120Hz) and ground reaction forces (sample rate 1200Hz) will be used to calculate external joint moments via inverse dynamics (Besier et al., 2003). The primary variables of interest are the peak external KAM (Nm/(BWxHT) %) and KAM impulse (Nm.s/(BWxHT) %), both normalised for body weight times height. The test-retest reliability of the UWA model for the external frontal plane moment curve during walking is 0.75 (coefficient of multiple determination, *r*^
*2*
^) [55]. Additional outcome measures that can influence the KAM during the stance phase will also be assessed, including frontal plane alignment of the tibia, peak external knee flexion moment, trunk lean in the frontal plane and internal foot rotation.

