## Discussion

There is a need to assess the effect of neuromuscular exercise on knee joint loading [66]. Neuromuscular exercise is known to improve knee articular cartilage quality, physical function and patient-reported outcomes [43,59] demonstrating its potential benefits in rehabilitation post-APM. However, the effects of neuromuscular exercise on medial knee joint load in people at risk of developing knee OA or showing early signs of knee OA has yet to be rigorously determined. The peak external KAM was chosen as a primary outcome during normal pace walking for two reasons. Firstly, this parameter has been previously shown to be elevated post-APM relative to healthy controls [18] and secondly because of its association with medial compartment knee joint load and knee OA progression [20,25]. The peak external KAM during a one-leg rise is also included as a primary outcome considering it is a challenging task that pilot research has shown can be reduced following a neuromuscular training intervention [36]. Overall, two parameters of KAM are of interest, the peak KAM and KAM impulse during tasks of varying difficulty (walking, one-leg rise, one-leg hop for distance). These tasks were chosen to determine if medial knee joint load regardless of task can be reduced following this neuromuscular program. Due to the time demands on the participants for laboratory testing, muscle strength and muscle activity assessment will only be taken from the previously operated leg. Objective and self-report measures of function, as well as self-reported measures of symptoms will provide clinically relevant information and allow comparison with other studies. Overall, this study will comprehensively quantify the effects of neuromuscular exercise on biomechanical, functional and clinical measures associated with knee OA in a population at increased risk of developing knee OA or progressing early OA.

A major strength of this study is the pragmatic approach of treatment delivery by multiple community-based physiotherapists. This delivery approach ensures that findings will be reproducible and generalisable and if found effective, will provide sound evidence for a feasible APM rehabilitation option.

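### Two primary outcomes are each tested at 5% with no rule for combining them, and the sample size allows for only one test

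*Protocol article*

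**What the plan says.** The article's Abstract (Methods/design) states: "The primary outcomes are change in the peak external knee adduction moment measured by 3-dimensional analysis during normal paced walking and one-leg rise". Table 2 lists the same two, and the Discussion justifies each in turn: "The peak external KAM during a one-leg rise is also included as a primary outcome". The Primary hypothesis section has one hypothesis about medial load, "as characterised by the peak external KAM during normal pace walking and one-leg rise".

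Data and statistical analysis applies one rule to everything: "All tests will be two-tailed and performed at the 5% significance level". No hierarchy, alpha split, adjustment or co-primary rule appears.

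Sample size uses one peak KAM effect, "a 10% reduction equates to an absolute change of approximately 0.2 Nm/(BWxHT")%, with a change-score SD of 0.3. It does not say which task these describe. It arrives at 27 evaluable per group "between the groups with 80% power (2 sided test, alpha=0.05"), and 31 after attrition. A parallel calculation is given for KAM impulse, which Table 2 lists as secondary.

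**The concern.** With one hypothesis and two tests, someone has to decide what a positive trial is. The article leaves that open while fixing the level of each test and the power of one.

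The question is practical. The Background reports that the uncontrolled pilot in 13 people with knee osteoarthritis found a 14% fall in peak KAM during one-leg rise and no difference in walking. If this trial repeats that pattern, the plan does not say whether its primary hypothesis is supported. A rule chosen after the results are known could be chosen to suit them.

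**Working it through.** **Inputs.** Two primary outcomes; two-sided alpha 0.05 for each; stated power 80%; peak KAM difference 0.2, SD of change 0.3; 27 evaluable per group. All come from the Abstract, Sample size, and Data and statistical analysis sections. The correlation r between the two test statistics is not given. It is assumed here, from 0 to 0.9.

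**1. The plan's own figure.** n per group = 2(1.960 + 0.842)² × (0.3/0.2)² = 2 × 7.85 × 2.25 = 35.3, so 36 (37 with the t distribution), not 27. At 27 per group the standard error is 0.3 × √(2/27) = 0.0816 and 0.2/0.0816 = 2.449. Power is Φ(2.449 − 1.960) = 69% (67% with t). The stated 80% is therefore not reproduced for even one outcome. Because that is a separate error, the effect of having two outcomes is shown first with 80% per test granted.

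**2. Either outcome counts.** At independence the familywise error is 1 − 0.95² = 0.0975. For r > 0 it is 1 − P(|Z₁| < 1.96 and |Z₂| < 1.96) from the bivariate normal.

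**3. Both outcomes required.** Type I error is at most 5%. Joint power is the bivariate normal probability that both tests succeed: 0.80² = 0.64 at independence with 80% per test, and 0.688² = 0.473 with the article's inputs.

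| r | Error if either counts | Joint power, 80% per test | Joint power, article's inputs, 27 per group | Evaluable per group for 80% joint power (0.2/0.3) |
|---|---|---|---|---|
| 0 | 9.75% | 64% | 47% | 47 |
| 0.3 | 9.5% | 67% | 51% | 46 |
| 0.5 | 9.1% | 69% | 54% | 45 |
| 0.7 | 8.4% | 71% | 58% | 43 |
| 0.8 | 7.8% | 73% | 60% | 42 |
| 0.9 | 7.0% | 75% | 62% | 40 |

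**4. Either outcome, with the error controlled.** The first step of Holm tests at 0.025 (critical value 2.241). Power for one outcome at 27 per group is Φ(2.449 − 2.241) = 58%. For 80%, n = 2(2.241 + 0.842)² × 2.25 = 42.8, so 43 evaluable per group.

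**The case against.** **The strongest reply** is that the hypothesis joins the two tasks with 'and', and that the Discussion speaks of reducing load regardless of task. The natural reading is then that both are required, and type I error is controlled. Testing each outcome at 5% is also compatible with a both-required or fixed-order rule, which an analysis plan could state. This stands as far as it goes: the inflated error applies only if either outcome suffices. But the article does not state the both-required rule, and under it the stated 80% is not the power for the primary hypothesis at any correlation below 1.

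A reader might also infer several stronger things that the document does not support:

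- *That the error is close to 10%.* That is the independence value. The two outcomes are the same moment in the same people and are probably positively correlated.
- *That the fall to 47–62% is due to having two outcomes.* Much of it is the sample-size error. From 80% per test the fall is to 64–75%.
- *That counting both legs makes four tests and an error of 18.5% (1 − 0.95⁴).* The article describes data collection, for example "three trials will be recorded and averaged for each leg", but nowhere plans primary tests on both legs. Independence between the legs of one person is also implausible.
- *That KAM impulse is a further primary outcome.* The External knee adduction moment section says "The primary variables of interest are the peak external KAM (Nm/(BWxHT) %) and KAM impulse (Nm.s/(BWxHT" and so on, but that sentence can be read as setting the KAM variables apart from the additional measures named later in the section. Impulse is secondary wherever outcome status is assigned.
- *That a split result is the most likely one.* The pilot was small and uncontrolled, and in a different population. If the article's effect holds for both tasks at 27 per group, both significant is more likely than exactly one (47% against 43% at r = 0; 54% against 29% at r = 0.5). A split is foreseeable, no more.

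**Conclusion.** The concern holds. As written, the 5% level for each test and the single-test sample size leave the primary hypothesis with one of two faults: a familywise error of about 7.0% to 9.75% if either outcome suffices, or joint power of 64% to 75% instead of 80% if both are needed. Both ranges run over assumed correlations from 0 to 0.9, and the power range grants the stated 80% per test. With the article's own 0.2, 0.3 and 27 per group, each test has about 69% and joint power is 47% to 62%.

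Baseline adjustment, which the analysis section plans, could recover some power. The sample-size section does not rely on it, and the residual SD would have to be about 0.26 instead of 0.3 for 27 per group to give 80% on a single test.

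**What to change.** Before unblinding, state one success rule in Data and statistical analysis, and restate the power in Sample size under it:

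- **Fixed sequence.** Pre-specify the order and test the second outcome at 5% only if the first is significant. The first test keeps the full 5%, but the second outcome cannot be claimed if the first fails. The Discussion gives reasons for each task, so the order is for the trial team to choose and justify.
- **Holm across the two.** Either outcome can be claimed, but the first step at 0.025 has about 58% power for one outcome at 27 per group, and 80% needs 43 evaluable per group.
- **Both required.** This is closest to the wording of the hypothesis and needs no alpha adjustment, but the stated power falls as shown, and 80% joint power needs 40 to 47 evaluable per group.

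The rule itself costs a few sentences. Those sentences do not restore power, so the restated figure should be reported plainly even if recruitment cannot be increased.

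As a minor clarification, name the leg used in the primary analysis, and align the wording of the External knee adduction moment section with Table 2, where KAM impulse is secondary.
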